#### Secondary outcomes

The secondary outcome measures are as follows:The VSS at 1 and 3 months after treatmentThe VSS will be also evaluated at 1 and 3 months after treatment. The differences in the 1st and 3rd month will also be compared among the three groups.Wound healingWound healing status will be assessed 14 days after surgery using the REEDA scale. The REEDA scale contains five variables: redness, edema, ecchymosis, discharge, and the approximation of wound edges [19].Erythema and pigmentationThese will be measured using a narrowband reflectance spectrophotometer (Mexameter MX18) at 1, 3, and 6 months after treatment.Scar thickness and areaThe scar thickness and area will be measured using a high definition ultrasound device at 1, 3, and 6 months after treatment.Meanwhile, the mother’s milk will be collected at each visit and immunoglobulins (IgG, IgA, IgM) and complements (C3, C4) will be detected by the transmission immune turbidity method using an automatic biochemical analyzer.Participants’ satisfaction of the treatment will be measured using a satisfaction scale, including five categories, namely, none, slight, moderate, good, and very good.The number of hypertrophic scars and wound infections during the 6 months.Safety and tolerability of the intervention.

All adverse events, including side effects and other ailments, will be recorded in a case report form. The researcher will report all adverse events to the ethics committee. For all participants, additional services arising from all adverse events will be provided free of charge.

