### Sample size

Our sample size calculation is based on previous results from [name] preliminary trial in Taipei Medical University WanFang Hospital [42]. These results found that the mean VSS was 4.50 ± 1.68 in healthy pregnant women. The ratio of the MSC and control group sample size sets was 2:1. We will use the conventional values *α* = 0.05 and *β* = 0.1 for two-sided tests of probability. Meanwhile, we hypothesize that the difference in mean VSS at 6 months after treatment between the MSCs and placebo group will be *δ* = 1.5. The total sample size is estimated to be 74. Considering a dropout and other potential influencing factors, the final participant is estimated to be about 90 (*n* = 30 in each group).

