### Statistical analysis

All analyses will be conducted on the intention-to-treat and per-protocol principles. Regardless of whether participants received the randomized treatment, the intention-to-treat principle considers all of them as randomized. A complete case analysis will be performed if missing data for the randomized participants accounts for less than 5% of total data. Multiple imputations will be used if missing data is more than 5%. Dropouts will be included in the analysis by multiple imputations for missing data. The effect that the per-protocol participants and missing data might have on results will be assessed via sensitivity analysis. Subgroup analysis will be performed based on age and gestational age.

The primary comparison, both doses vs. placebo, will be analyzed using a superiority analysis. We will use the *t* test for the continuous outcome. Meanwhile, high dose vs. placebo and low dose vs. placebo will also be analyzed using the *t* test. Other outcomes will be analyzed using noninferiority analysis. The mean (and standard deviation) will be expressed for continuous variables, and numbers (percentages) will be expressed for categorical variables. Group variances will be compared using Leven’s test at the 0.05 significance level. Analysis of variance (ANOVA) will be used to analyze continuous data, and the *chi*-square test or Fisher’s exact test will be used for categorical data. To investigate the effects of treatment and time course, repeated measures ANOVA will be applied to determine changes in the continuous outcome data at each visit. R 3.1 software will be used for analysis.

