Although previous results of trials with MSCs in wound healing have been reported, the application of MSCs on Cesarean section skin scars has not yet been investigated. In this prospective, randomized, double-blind, placebo-controlled study, we aim to investigate the possible effects of MSCs in women’s skin scars after Cesarean delivery. We hypothesize that MSCs can enhance wound healing, reduce hypertrophic skin scars, and decrease wound infection. To our knowledge, this trial is the first to investigate the potential of the therapeutic use of MSCs for the management of women’s skin scars after Cesarean delivery. The outcomes from this trial will help to determine the efficacy and safety of MSC treatment in Cesarean section skin scars. The results will also identify a therapeutically effective dose of MSCs in preventing hypertrophic scars and wound infections risk factors. It will give us an effective therapeutic strategy to combat Cesarean section skin scars, even with uterine scarring.

A limitation of this trial is that this is a single-center clinical trial, which will limit the extrapolation of results. Meanwhile, loss of participants at follow-up is possible, especially for nonresponders in the prospective trial study. Notwithstanding its limitations, this trial will suggest whether MSC can be a safe and effective in the treatment of Cesarean section skin scars.

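### No MSC-versus-placebo superiority contrast is expressly assigned to the secondary efficacy outcomes, so the noninferiority label and the three-group tests do not directly test the benefit hypotheses

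*Protocol article*

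**What the plan says.** - **Primary outcome.** The Statistical analysis section states: "The primary comparison, both doses vs. placebo, will be analyzed using a superiority analysis". It names a t test and adds high dose versus placebo and low dose versus placebo, also by t test. The Sample size section uses the same pooled contrast: "The ratio of the MSC and control group sample size sets was 2:1".
- **Secondary VSS.** Under Secondary outcomes, for months 1 and 3: "The differences in the 1st and 3rd month will also be compared among the three groups".
- **Framework for the rest.** The Statistical analysis section puts outcomes other than the primary under a noninferiority analysis. Shortly afterwards it says "Analysis of variance (ANOVA) will be used to analyze continuous data", with chi-square or Fisher's exact test for categorical data, and repeated measures ANOVA for treatment and time effects.
- **Hypotheses.** The Discussion says "We hypothesize that MSCs can enhance wound healing, reduce hypertrophic skin scars, and decrease wound infection". The end of the Background makes the same directional claim for scars and infections. The Discussion also aims to identify an effective dose.

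**The concern.** The trial's hypotheses about wound healing, hypertrophic scars and infection are all of the form that MSCs do better than placebo. Two frameworks are named for these outcomes, and neither answers that question directly.

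- **Noninferiority to placebo** can at most show that MSCs are not unacceptably worse. A benefit hypothesis needs a superiority comparison.
- **A three-group ANOVA or chi-square test** has 2 degrees of freedom and asks whether any arm differs from any other. It can be significant because the two doses differ from each other, without showing that either beats placebo. It can also miss a benefit shared by both doses that a pooled contrast would detect.

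The two frameworks also do not fit together. Noninferiority needs a named pairwise comparison with placebo, which a three-group test does not supply. As the text stands, the choice between three-group, pooled and per-dose results for each secondary outcome could be made after the data are seen.

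**Working it through.** **1. Test against hypothesis, outcome by outcome**

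| Outcome | Framework or test named | Question stated | MSC-vs-placebo superiority contrast expressly assigned? |
|---|---|---|---|
| VSS, month 6 | Superiority t tests, pooled and per dose | MSC better than placebo | Yes |
| VSS, months 1 and 3 | Three-group comparison; noninferiority; ANOVA | MSCs reduce scars | No |
| Wound healing (REEDA) | Noninferiority; test by data type | MSCs enhance healing | No |
| Hypertrophic scars, infections | Noninferiority; chi-square or Fisher | MSCs reduce both | No |

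**2. Inputs for the power comparison**

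From the Sample size section: "We will use the conventional values *α* = 0.05 and *β* = 0.1 for two-sided tests of probability"; 30 per arm; SD from "the mean VSS was 4.50 ± 1.68 in healthy pregnant women"; and a difference "between the MSCs and placebo group will be *δ* = 1.5". The only standardized effect in the document is therefore 1.5/1.68 = 0.893 SD, for month-6 VSS. No effect size is given for a secondary outcome, so the other values below are assumptions shown as a range.

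The plan gives no power figure for secondary outcomes to reproduce. Its one related figure is the primary total of 74. The stated inputs give placebo n = 1.5 × [1.68 × (1.960 + 1.282)/1.5]² = 19.8, so 20 + 40 = 60 in total. That mismatch is a separate matter and does not affect this point.

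**3. Formulas** (effects in SD units; n per arm; low-dose effect L, high-dose effect H)

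- Pooled contrast, 1 df: noncentral t with ncp = [(L + H)/2] / √(1/n + 1/(2n)), 87 df.
- Three-group F test, 2 df: noncentral F with λ = n × Σ(mean of arm − grand mean)², on 2 and 87 df.

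Example at n = 30 and L = H = 0.6. The ncp is 0.6/√(1/30 + 1/60) = 2.683, giving power 75.6%. The grand mean is 0.4, so λ = 30 × (0.16 + 0.04 + 0.04) = 7.2, giving power 65.2%.

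**4. Equal dose effects, 30 per arm, two-sided 5%**

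| Effect (SD) | Pooled contrast | Three-group F | Gain (points) |
|---|---|---|---|
| 0.40 | 42.4% | 33.0% | 9.4 |
| 0.50 | 59.9% | 48.9% | 11.0 |
| 0.60 | 75.6% | 65.2% | 10.4 |
| 0.65 | 82.0% | 72.7% | 9.3 |
| 0.70 | 87.2% | 79.3% | 7.9 |
| 0.893 | 97.7% | 94.9% | 2.7 |

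With 74 evaluable women and 0.893 SD the figures are 94.7% against 89.8%, a gain of 4.9 points.

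**5. Unequal dose effects, high dose 0.6 SD, 30 per arm**

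| Low dose as share of high | Pooled contrast | Three-group F | Difference (points) |
|---|---|---|---|
| 75% | 64.1% | 55.7% | +8.4 |
| 50% | 51.2% | 52.2% | −1.0 |
| 25% | 38.2% | 55.7% | −17.5 |
| 0 | 26.4% | 65.2% | −38.9 |

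High dose versus placebo alone, by t test with 30 per arm at 0.6 SD and unadjusted 5%, has 63% power whatever the low dose does.

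**6. Binary outcomes** (simulated chi-square, 30 per arm, 2×2 against 2×3; rates assumed, with 20% the top of the infection range quoted in the Background)

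- 20% vs 5% and 5%: 60% against 46%.
- 20% vs 10% and 10%: 28% against 18%.
- 20% vs 10% (low) and 3% (high): 48% against 43%.

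**The case against.** **The three-group reading is an inference.** The protocol never calls these tests omnibus. It assigns ANOVA and chi-square by data type, not by outcome tier, and does not expressly confine the per-dose t tests to the primary. The Primary outcome section uses the same three-group wording for month-6 VSS, which is then analysed by pooled and per-dose contrasts. A reader might infer that months 1 and 3 are certainly tested for a different question from month 6. The document does not establish that. What stands is that the three-group wording is resolved by a named contrast for the primary and is not resolved for the secondaries. In addition, a t test cannot serve the scar and infection counts.

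**The cost is easily overstated.** A reader might infer a general loss of about 10 power points. That needs equal dose effects of roughly 0.4 to 0.65 SD, and the document gives no secondary effect size. At the one effect it states, the difference is 2.7 points.

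**The pooled contrast can be the weaker test.** The low-dose arm receives cells on three days and placebo on the next three, so unequal effects are plausible, and finding an effective dose is a stated aim. This objection stands, and it is why per-dose contrasts must be reported beside the pooled one.

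**Detail may sit elsewhere.** Three-group tests are conventional in a three-arm Phase II trial, and follow-up contrasts are often left to a fuller document. That would answer a complaint about omission. It does not answer the express noninferiority sentence, which conflicts with the benefit hypotheses.

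**Conclusion.** The point holds in a limited form. No superiority contrast is expressly assigned to any secondary efficacy outcome. The noninferiority framework and the named tests, on their most natural reading, do not directly test the stated hypotheses of benefit. The conflict between noninferiority and those hypotheses is on the page; the 2-df reading is a reasonable inference.

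The power effect is a conditional range and carries less weight than the mismatch of question and test. With 30 per arm it runs from a gain of about 11 points (equal doses, 0.5 SD), through about 3 points (equal doses, 0.893 SD) and about nil (low dose half as effective), to a loss of about 39 points (low dose inert, high dose 0.6 SD). All of these assume normal outcomes with common variance and an unadjusted two-sided 5% level. The change is worth making because it needs only wording. The primary analysis is not affected.

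**What to change.** In the Secondary outcomes and Statistical analysis sections:

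1. For the secondary efficacy outcomes, replace the noninferiority sentence with superiority contrasts matching the primary: both doses versus placebo first, then high versus placebo and low versus placebo, each with a confidence interval.
2. Use 2×2 tables for hypertrophic scars and for wound infections, pooled and per dose.
3. Keep the three-group ANOVA and the chi-square or Fisher test as supportive.
4. If noninferiority was meant for particular outcomes, such as safety measures, name them and limit the sentence to those.

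**Cost:** wording only, with no new data or visits; it should be settled before unblinding. The downside is that the pooled contrast loses power to the three-group test once the low dose has less than about half the high-dose effect. The per-dose contrasts largely cover this (63% for high dose versus placebo at 0.6 SD, against 65% for the F test with an inert low dose). They do add tests, so the per-dose results should not be presented alone.

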### Sample size

Our sample size calculation is based on previous results from [name] preliminary trial in Taipei Medical University WanFang Hospital [42]. These results found that the mean VSS was 4.50 ± 1.68 in healthy pregnant women. The ratio of the MSC and control group sample size sets was 2:1. We will use the conventional values *α* = 0.05 and *β* = 0.1 for two-sided tests of probability. Meanwhile, we hypothesize that the difference in mean VSS at 6 months after treatment between the MSCs and placebo group will be *δ* = 1.5. The total sample size is estimated to be 74. Considering a dropout and other potential influencing factors, the final participant is estimated to be about 90 (*n* = 30 in each group).

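### The total of 74 does not follow from the stated sample-size inputs, which give about 60 to 63 for 90% power; inputs and output must be reconciled

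*Protocol article*

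**What the plan says.** The Sample size section of the protocol article gives every input that a two-group comparison of means needs:

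- Variability: "These results found that the mean VSS was 4.50 ± 1.68 in healthy pregnant women".
- Effect: the difference in mean VSS at 6 months "between the MSCs and placebo group will be *δ* = 1.5".
- Allocation: "The ratio of the MSC and control group sample size sets was 2:1".
- Error rates: "We will use the conventional values *α* = 0.05 and *β* = 0.1 for two-sided tests of probability".
- Result: "The total sample size is estimated to be 74".
- Loss allowance, added after that result: "Considering a dropout and other potential influencing factors, the final participant is estimated to be about 90", with 30 in each group.

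The Statistical analysis section names the comparison to which the calculation belongs: "The primary comparison, both doses vs. placebo, will be analyzed using a superiority analysis". It also names the test: "We will use the *t* test for the continuous outcome".

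**The concern.** The calculation should be reproducible from the page, because the inputs, the comparison and the test are all printed and agree with one another. It is not. The printed total exceeds what the inputs require by 11 to 14 women, which is more than rounding can explain. At least one of the printed items (alpha, beta, the SD, the difference, the test or the total) is therefore not what was used. A reader cannot tell from the text what power the trial was designed for, or how many evaluable women that power needs.

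**Working it through.** **Inputs.** SD 1.68 (the ± figure read as an SD; the text does not label it), difference 1.5, MSC:placebo 2:1, two-sided alpha 0.05 and beta 0.1, all from the Sample size section. The two-sample t test of both doses against placebo is from the Statistical analysis section.

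**1. Normal formula with the stated inputs.** For 2:1 allocation,

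n(placebo) = (1 + 1/2) × (z for alpha + z for beta)² × SD² / difference²

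= 1.5 × (1.960 + 1.2816)² × 1.68² / 1.5² = 19.77.

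The total is 3 × 19.77 = 59.3, so 20 + 40 = **60**. The stated 74 is not reproduced.

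**2. Noncentral t with the stated inputs.** The noncentrality is 1.5 / (1.68 × √(1/n₁ + 1/n₂)), with n₁ + n₂ − 2 degrees of freedom.

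| MSC : placebo | Total | Power |
|---|---|---|
| 40 : 20 | 60 | 89.4% |
| 41 : 20 | 61 | 89.6% |
| 40 : 21 | 61 | 90.3% |
| 41 : 21 | 62 | 90.6% |
| 42 : 21 | 63 | 90.8% |
| 49 : 25 | 74 | 94.8% |
| 60 : 30 | 90 | 97.7% |

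The requirement for 90% power is **61 to 63**: 61 if the ratio may be rounded to 40:21, and 63 if it must be exactly 2:1. The gap to 74 is 74 − 63 = 11 to 74 − 60 = 14 women.

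**3. What would give 74, or nearly so?** Each of these changes something that the article states.

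- *Beta 0.05, normal formula:* 1.5 × (1.960 + 1.645)² × 1.68² / 1.5² = 24.45 placebo. The total is 73.35, which rounds up to 25 + 49 = 74.
- *Two-sided alpha 0.025, beta 0.1, noncentral t:* 74 has 90.2% power at 50:24 and 90.8% at 49:25. Over rounding choices and formulas, this route gives 72 to 75.
- *Three-group F test at alpha 0.05, both doses 1.5 below placebo:* 25 per arm, 75 in total, has 90.2% power.
- *Beta 0.1 with another SD or difference, normal formula:* 74 needs an SD of about 1.88 or a difference of about 1.34.

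**4. What does not explain it.**

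- *One-sided alpha 0.05* lowers the total to 50 or 51.
- *Three arms sized by 1:1 pairwise tests* need 81 to 84.
- *A rank-test efficiency correction* gives 63 to 72, and the article specifies a t test.
- *Dropout* is applied after the 74: going from 90 to 74 is a loss of (90 − 74)/90 = 17.8%.

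**The case against.** **The error is harmless.** Enrolment of 90 exceeds every version of the requirement, and no allocation, test or recruitment target changes. This stands, and it limits the point to a correction of the text. It does not make the paragraph right, because a stated power and total that disagree with their own inputs are wrong as written.

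**The 74 may be sound and only an input misreported.** An alpha of 0.025 would land on 74. A three-group F test would land one above it, and the article does speak of comparing VSS among three groups and of analysis of variance for continuous data. This also stands as a possibility. It is why the point cannot go beyond saying that the inputs and the total disagree.

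Three stronger readings are tempting, and the article does not support them:

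- *A reader might infer that beta was halved, or that beta or the total must be the faulty item.* The exact match at beta 0.05 is suggestive, but the alternatives come too close to exclude. Writing beta 0.05 without knowing could put a false rationale into the protocol.
- *A reader might infer that the trial is underpowered.* The discrepancy runs the other way.
- *A reader might count the power of each single dose against placebo as part of the error.* The 90% is stated only for MSCs against placebo. The single-dose tests are additional analyses for which the article claims no power, so a lower figure for them contradicts nothing.

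**Conclusion.** The point holds as an inconsistency in the sample-size statement. The printed inputs require 60 (normal formula) or 61 to 63 (noncentral t) for 90% power, and the article states 74, which is 11 to 14 more. At 74 evaluable, the pooled comparison has about 95% power. At 90 enrolled with no loss, it has about 97.7%.

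These figures assume that 1.68 is an SD common to both groups, that the true difference is 1.5 and that evaluable women stay close to 2:1. The article does not show which item is wrong. The error is conservative and is one of reporting and reproducibility; it does not put the primary comparison at risk.

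**What to change.** Keep 90 enrolled and correct the Sample size section so that inputs and output agree. Use whichever of these is true:

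1. State that 74 evaluable women give about 95% power at two-sided alpha 0.05.
2. State that about 61 to 63 evaluable women are needed for 90% power, and present 90 as the enrolment that allows for loss.
3. If a different alpha or test produced 74, state it, and make it consistent with the Statistical analysis section.

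The sponsor should go back to the original calculation before choosing. The cost is a correction to one paragraph, and under the third option possibly a matching sentence in the Statistical analysis section.

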### Randomization, concealment, and blinding

A computerized random number generator will be used to produce a randomization schedule employing simple randomization by an independent clinical researcher, who is not involved in the recruitment, intervention, assessment, or statistical analysis. During the study period, the independent clinical researcher will retain the randomization list. The randomization sequences will be concealed in lightproof, sealed envelopes. After signing informed consent forms, eligible participants will be randomly allocated to the three parallel groups at a 1:1:1 allocation ratio, according to the randomization list.

Each participant will receive a unique randomized number. Meanwhile, each participant’s pump will be labeled with a unique randomization number, which will become the participant’s number. Direct participants and investigators, including the outcome assessors and statisticians, will be blinded to the allocation status throughout the study. Once participants have been allotted randomized numbers, a reasonable effort will be made by investigators to avoid missing data.

### Data collection and management

All research investigators will be trained uniformly in standard operating procedures. A regular monitoring scheme will be set up to collect accurate and valid data. Non-numeric data will be converted into numbers for storage. All laboratory specimens will be identified only by a coded identification number to maintain participant confidentiality. To ensure confidentiality, data dispersed to project team members will be blinded to any identifying participant information. After verification of the content, two research investigators will independently input the data into a database. All participant information will be kept safely under confidential conditions and archived for 10 years. The project principal investigator could access the full data. Participant recruitment is currently in progress. The first participant was recruited on 14 September 2016.

Meanwhile, a data monitoring committee will be established, which will be independent of the study organizers and will periodically review the accumulating data and determine whether the trial should be modified or discontinued. The committee members will perform independent review of trial processes every 2 months.

